### Recruitment {15}

In alignment with past approaches in Australia and the European Centre for Disease Prevention and Control protocol, all patients admitted to the ward before or at 08:00 h on the first survey day and not discharged from the ward at the time of the survey will be eligible and will be evaluated for a HAI. Patients transferred in or out after 08:00 h will not be included. Patients will be excluded if they are under 18 years of age or are due to have same-day treatment or surgery.

## Assignment of interventions: allocation

### Sequence generation {16a}

There will be two wards allocated to each cluster. The allocation of when each cluster will commence the intervention will be randomised using Microsoft Excel. This will be undertaken by the study statistician, not involved in data collection or the determination of outcomes. The equipment to be tested in the FM audit will be randomised using Microsoft Excel to ensure a variety of shared medical equipment is audited. This will be undertaken by one member of the research team, not involved in data collection or the determination of outcomes.

### Concealment mechanism {16b}

Once randomisation has occurred and each ward is allocated into a cluster, this information will be kept by the person undertaking randomisation on their own (work) computer. This allocation will not be available to the participating wards or PSAs or those involved in data collection. Each participating ward and PSAs will be informed of the cluster allocation 2 weeks prior to the commencement of the intervention of that cluster. This concealment process will be undertaken by the person undertaking the randomisation informing the trial coordinator of the allocation, as per the timing above. The trial coordinator will then inform the ward and PSAs.

### Implementation {16c}

The allocation sequence will be generated by the study statistician and each ward will be randomly assigned to a cluster. As each cluster enters the intervention phase, the trial coordinator will facilitate PSA training sessions and auditing feedback.

## Assignment of interventions: blinding

### Who will be blinded {17a}

The researcher collecting the data on the primary outcome (HAI data) will be blinded to the intervention (i.e. knowing whether the ward is an intervention or control ward). Similarly, the researcher collecting FM audit data will be blinded to the intervention. Results of the audit process will not be made available to wards in the control phase of the study.

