## Trial design {8}

This study is a stepped wedge randomised controlled study, conducted in 10 wards of one acute Australian hospital over 36 weeks. A stepped wedge design allows all wards to receive the intervention at different times, with each ward acting as its own control. Each cluster will comprise two wards. One cluster will switch to the intervention every 6 weeks. This study design reduces the influences of confounders such as variations in size and case mix and supports feasibility while maintaining rigour. This design also allows research staff to work with individual wards as they adopt the intervention, maximising consistency of intervention and aiding implementation (Fig. 1).

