#### Additional cleaning

During the intervention phase, each trial ward will receive an additional 3 h of cleaning per weekday by dedicated cleaners. This is in addition to routine cleaning that already occurs. The use of dedicated cleaners will reduce the risk of contamination and assist in consistency in implementation. An expression of interest process will be used to identify cleaners who are seeking additional work. This will be managed and handled by the participating hospital, in line with enterprise bargaining arrangements and local policy.

The additional cleaning will focus on specific shared medical equipment (Table 1). The use of a Therapeutic Goods Administration (TGA)-registered dual detergent-disinfectant wipe effective against a range of bacteria and viruses will be used for additional cleaning. The fidelity of the additional cleaning will be measured using the fluorescent markers (see the ‘Audit and feedback’ section). In addition, items that have been cleaned but remain in storage until use will be labelled as cleaned, using bright labelling. This will enable clinical staff to easily identify which equipment is clean and ready for use.

**Table 1 Tab1:** Focus of additional cleaning

Type of equipment	Additional detail	Frequency	Estimated time
Intravenous drip stand/pole	Those in use by patients	Daily	5 min
	Those in the storage on the ward	Daily	10 min
Infusion pump(s)	Those *not in use* by patients. Areas to be cleaned include all external surfaces daily	Daily	10 min
Mobile blood pressure machines	Automatic machines Areas to be cleaned are cuff, buttons, O_2_ probe, temperature probe, and storage basket	Daily	30 min
Computer on wheels (approx. 10–15 per ward)	Surfaces to be cleaned include: • Horizontal surfaces • Keyboards • Vertical surface and pedestals	Daily Daily Weekly	60 min
Commodes	All surfaces to be cleaned, focus on handles and seat	Daily	20 min
Blood glucose machine	Machines include those in a box and the smaller glucose machines. Focus on cleaning surfaces	Daily	10 min
Mobility equipment	Focus on cleaning frequency touch areas, e.g. handles. Those in storage/shared areas, i.e. not those kept in patient rooms	Daily	20 min
Total			165 min

^Note that if time allows, other equipment will include trolleys, bladder scanners (cleaning probe and buttons), patslides (those in shared areas/storage only), resuscitation trolleys (top surface and drawers—outside only) and medication trolleys

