#### Audit and feedback

The benefits and role of audit, including the use of fluorescent markers (FM), in assessing environmental cleaning, is well documented (7,13,14). Audit and feedback to the cleaning staff involved in the additional cleaning will include the use of FM technology, in which invisible gel dots that are removed by cleaning are applied to surfaces. The dots are invisible to the naked eye, resist dry abrasion, and are removed completely by routine cleaning. A structured auditing approach, with staff feedback underpinned by education, will aid improvements in cleaning, as shown in multiple studies (7,13,14). FM auditing of shared equipment will be conducted fortnightly in each ward.

During the intervention phase, audit results will be reported verbally to the cleaning staff, with a follow-up email to cleaning supervisors and the Nursing Unit Managers. Audit results will be used to inform further informal face-to-face education and training. In discussing audit results, informal goals for the next audit will be set with the cleaners. Additional reports will be provided for internal committees, such as the Infection Prevention and Control committee at the conclusion of the study.

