## Data collection and management

### Plans for assessment and collection of outcomes {18a}

A data extraction tool has been developed and piloted in REDCap®. This tool was adapted from a previous multi-centre point prevalence study (1). The researcher responsible for collecting the data will be trained in the use of the survey instrument to extract relevant data pertaining to the intervention and relevant outcomes. After reviewing medical records, pathology and microbiology databases, the researcher will determine if the patient has a HAI. The determination of a HAI will be undertaken through an algorithm applying the HAI definitions in the ECDC protocol (16). Data on each HAI identified will be consistent with the ECDC protocol. The attribution of a HAI to a ward will be determined through the use of a 48-h time frame, i.e. the infection symptom onset must occur > 48 h after admission to the ward, for it to be attributable to the ward. If a patient is transferred to a ward and a HAI is identified within 48 h of transfer, it will be attributed to the previous ward. An interrater reliability assessment will be independently undertaken to validate the accuracy of HAI determinations (1).

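### The fluorescent-marker auditor is stated to be blinded, but labels placed on shared equipment in the intervention phase can reveal a ward's phase; blinding of the HAI assessor is not secured

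*Protocol article*

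**What the plan says.** Section {17a} of the protocol article makes two unqualified statements: "The researcher collecting the data on the primary outcome (HAI data) will be blinded to the intervention" and "Similarly, the researcher collecting FM audit data will be blinded to the intervention". Section {16b} withholds the allocation from those who collect data.

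Other sections describe what each assessor meets in practice.

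- **Labels.** Additional cleaning ({11a}) says: "During the intervention phase, each trial ward will receive an additional 3 h of cleaning per weekday by dedicated cleaners". As part of that activity, "items that have been cleaned but remain in storage until use will be labelled as cleaned, using bright labelling".
- **FM audit.** Audit and feedback says: "FM auditing of shared equipment will be conducted fortnightly in each ward". The equipment to be tested is picked at random by a team member outside data collection ({16a}).
- **HAI determination.** Section {18a} says: "After reviewing medical records, pathology and microbiology databases, the researcher will determine if the patient has a HAI". This is done through an algorithm with ECDC definitions, and "An interrater reliability assessment will be independently undertaken to validate the accuracy of HAI determinations". The same section has this researcher trained to extract data about the intervention as well as the outcomes.
- **Rollout.** Section {8} says: "One cluster will switch to the intervention every 6 weeks". There are ten wards in clusters of two, over 36 weeks.

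**The concern.** A stated blind should survive the assessor's own working conditions. The FM auditor has to find, mark and re-read shared equipment on the ward. Table 1 makes stored equipment a core target of the extra cleaning: stored drip stands, infusion pumps not in use, and mobility equipment in storage. The phase cue can therefore sit on the item being scored. Because wards never switch back, a single sighting settles that ward's phase for the rest of the trial.

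The HAI researcher is less exposed, but not clearly shielded. Section {18a} does not say that the review takes place off the ward. Wards are told their allocation two weeks before they switch ({16b}), dedicated cleaners are present on weekdays, and they speak daily with Nursing Unit Managers ({11c}). Extracting data about the intervention is hard to square with not knowing the phase.

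At stake is whether part of an estimated effect reflects scoring rather than cleaning, and whether the trial reports a blinded assessment that it did not fully have.

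**Working it through.** **1. Layout.** Fig. 1 is not shown, so the layout is inferred from {8} and {14}: 5 clusters, 6 periods of 6 weeks, one cluster switching at each boundary. The plan's total reproduces: 132 × 5 × 6 = 3,960. The share of clusters in intervention by period is 0/5, 1/5, 2/5, 3/5, 4/5, 5/5. Period 1 is all control and period 6 all intervention, so the date alone gives the phase in 5 + 5 = 10 of 30 cluster-periods, or 1,320 of 3,960 planned observations (33%). In periods 2 to 5 (20 of 30) a ward-specific cue is needed.

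**2. Who meets the label.**

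| | FM auditor | HAI researcher |
|---|---|---|
| Material assessed | Shared equipment, on the ward, fortnightly | Medical records, pathology and microbiology databases |
| Label in view? | Yes, on stored items cleaned in intervention wards | Not shown; place of review not stated |
| Other cue | Dedicated cleaners on the ward | Extracts data about the intervention |

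**3. Calendar knowledge and the primary effect.** Assume a scoring shift of +1 point in all wards in period 1 and −1 point in all wards in period 6, with no true effect. {20a} fits study time as categorical, with a linear term also tested.

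- Categorical time: a shift common to all wards in a period is absorbed by that period's effect. Bias 0.00 points.
- Linear time: the intervention share rises by exactly 1/5 per period, so once a line is fitted the intervention indicator sums to zero over wards in every period. Bias 0.00 points.

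A linear mixed-model calculation with 66 patients per ward-period and ICC from 0.01 to 0.3 gave 0.00 for both. A logistic fit with ward and period effects and shifts of ±0.2 on the logit scale returned an odds ratio of 1.000.

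**4. The same shift with no time term.** The FM model in the secondary outcome section lists a ward random intercept and intervention terms, but no calendar-time term. Take the binary intervention effect.

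- Within wards, each cluster contributes −1 to the numerator, giving −5 in total. The denominator is the sum of k(6 − k)/6 for k = 1 to 5: (5 + 8 + 9 + 8 + 5)/6 = 5.83. Bias = −5/5.83 = −0.86 points.
- With no ward variation, it is −(5 + 5)/15 = −0.67 points.
- The mixed-model calculation at ICC 0.01 to 0.3 gave −0.81 to −0.86.

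FM audit counts per ward are not stated; the two limits cover any equal count. For FM the expected direction is reversed: more dots scored as removed under intervention.

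**5. Phase known in the mixed periods.** Assume a 1-point shift in intervention wards.

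| Cells affected | Categorical or linear time | No time term |
|---|---|---|
| All intervention cells | −1.00 | −1.00 |
| Periods 2 to 5 only | −1.00 | −0.57 to −0.60 |

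Ward-specific knowledge therefore passes in full into a time-adjusted effect. For scale, the HAI target difference is 11% × 0.35 = 3.85 points. The documents give no comparable target for FM.

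**The case against.** The strongest reply is that the primary outcome is well protected. Allocation is withheld from data collectors, HAIs are determined from records and databases by an algorithm with external definitions, and an independent interrater check is planned. Nothing has the HAI researcher look at equipment. This stands. A reader might infer that HAI blinding cannot hold, but the documents show only that exposure is possible.

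A reader might also infer that knowing the phase in a third of cluster-periods biases the primary result. It does not, because the planned time effect removes a common shift. Nor should a bias in HAI prevalence be sized from assumed sensitivity and specificity: the documents give neither, and such figures would only restate the assumption.

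On the FM side, labels go only on stored items, the audited equipment is chosen by someone else, and the room for judgement in reading a dot is not stated. These points limit the likely size of bias. They do not restore the blind, since one label anywhere on the ward is enough. That control wards use no such labels is an inference from where the label is described; the protocol does not say so outright.

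A condensed article may leave the masking of the interrater check, or an FM time term, to a fuller document. Their absence is not the finding here.

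**Conclusion.** The point holds in full for the FM auditor and in part for the HAI researcher. For FM, {17a} claims a property that the described procedures do not give, in every period where labelled wards exist. For HAIs, blinding is not secured, and {17a} must be reconciled with the intervention-data extraction in {18a}.

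The actual bias cannot be sized from the documents. Per assumed 1-point shift, it is 1.00 point when the phase is known ward by ward. From the calendar alone it is essentially zero in the primary analysis, and 0.67 to 0.86 point in an FM model without a time term. The zero assumes equal ward sizes, an equal shift in all wards and phase coded by 6-week period; the one-week lag or unequal sizes could leave a small residue, mainly under linear time. If the full analysis plan puts study time in the FM model, the calendar part of the FM concern falls away. The label part does not.

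**What to change.** 1. Reword {17a}: assessors are not told the phase; FM blinding is partial; phase can be inferred from labels, and from the date in periods 1 and 6.
2. Add a field to the FM form for whether a label was present at marking and at reading. Include study time in the FM model. Add a sensitivity analysis restricted to items in use at audit, defined by the item's state at that moment because the same item moves in and out of storage. This removes the cue from the scored item, but not what the auditor has learned elsewhere on the ward, so report it as supportive only.
3. Make HAI determinations off the ward from the records and databases already named, and give extraction of intervention data to someone else in the study team.
4. For the interrater check already planned, balance the sample by phase and report agreement by phase. Give the second rater extracts with the ward name and calendar dates replaced by days relative to ward admission and survey day. Relative days are needed because the 48-hour attribution rule cannot be applied without them.

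The cost is protocol wording, one form field, a reassigned extraction task and some preparation of masked extracts. The restricted FM analysis will be less precise and leaves out equipment that is cleaned only when stored or not in use. Sample size and intervention are unchanged.

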### Procedure for unblinding if needed {17b}

Once data collection and statistical analysis have been finalised, the interventions can be unblinded for the purpose of interpreting the data.

## Data collection and management

### Plans for assessment and collection of outcomes {18a}

A data extraction tool has been developed and piloted in REDCap®. This tool was adapted from a previous multi-centre point prevalence study (1). The researcher responsible for collecting the data will be trained in the use of the survey instrument to extract relevant data pertaining to the intervention and relevant outcomes. After reviewing medical records, pathology and microbiology databases, the researcher will determine if the patient has a HAI. The determination of a HAI will be undertaken through an algorithm applying the HAI definitions in the ECDC protocol (16). Data on each HAI identified will be consistent with the ECDC protocol. The attribution of a HAI to a ward will be determined through the use of a 48-h time frame, i.e. the infection symptom onset must occur > 48 h after admission to the ward, for it to be attributable to the ward. If a patient is transferred to a ward and a HAI is identified within 48 h of transfer, it will be attributed to the previous ward. An interrater reliability assessment will be independently undertaken to validate the accuracy of HAI determinations (1).

### Plans to promote participant retention and complete follow-up {18b}

Not applicable—as patients are not recruited and there is no patient follow-up in this study.

### Data management {19}

The data which will be obtained from patients’ hospital medical record will be non-identifiable and there are clear processes in place to ensure that the privacy of data is maintained. These processes include appropriate storage of data in password-protected files and the destruction of these data after completion of the study. The data will be kept for a period of 5 years from the point of any publication relating to the research.

### Confidentiality {27}

No identifiable data is collected. The project is supervised and overseen by a clinician, registered with the Australian Health Practitioner Regulation Authority.

### Plans for collection, laboratory evaluation and storage of biological specimens for genetic or molecular analysis in this trial/future use {33}

There will be no biological specimens tested in this study.

To reduce the effect of confounders due to seasonality, viral respiratory infections (RSV, COVID-19, influenza) will be removed for the purpose of primary analysis. In addition, any HAI data related to an outbreak will be excluded from primary analysis. The study period is aligned to span over three full seasons (autumn, winter, spring), with the study midpoint corresponding to the usual epidemiological peak for respiratory infection in the region. Additionally, the use of historical coding data can identify underlying trends over recent years.

#### Secondary outcome analysis

##### FM
audits

We will analyse data from fortnightly cleaning audits using a binomial generalised linear mixed model with a logit link function on the proportion of equipment that were deemed ‘cleaned’. A random intercept will be included for each ward. The effect of the intervention will be tested in three ways: a binary intervention effect, to model an immediate improvement in cleaning; a linear intervention effect, defined as weeks after each ward’s intervention start date, to model a more gradual improvement over time; and a combined binary–linear intervention effect. As per the analysis of the primary outcome, the intervention effect will switch from ‘no’ to ‘yes’ 1 week after the start of the intervention period.

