### Outcomes {12}

The primary outcome is the proportion of inpatients aged ≥ 18 years old with a HAI as measured by a HAI point prevalence study (PPS). The secondary outcomes are the thoroughness of cleaning as being the proportion of dots that were completely removed, as measured by the FM gel and ultraviolet light system, and the cost-effectiveness of the intervention compared with routine cleaning.

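### The cleaning-audit model omits equipment type although it is known for every audited item; if types differ, this costs power for a modest effect, without bias

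*Protocol article*

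**What the plan says.** The secondary analysis section on FM audits fits its model "using a binomial generalised linear mixed model with a logit link function on the proportion of equipment that were deemed" cleaned. It names one grouping term: "A random intercept will be included for each ward". The intervention is coded in three ways, starting with a binary effect: "The effect of the intervention will be tested in three ways: a binary intervention effect, to model an immediate improvement in cleaning". The other two are a linear effect and a combined effect. No equipment-type term is named. The beta-binomial alternative for over-dispersion is listed for the primary outcome and is not carried over to the audits.

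On the choice of what to audit, Sequence generation {16a} states: "The equipment to be tested in the FM audit will be randomised using Microsoft Excel to ensure a variety of shared medical equipment is audited". The person drawing the sample is independent of outcome assessment: "This will be undertaken by one member of the research team, not involved in data collection or the determination of outcomes". On frequency: "FM auditing of shared equipment will be conducted fortnightly in each ward".

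On the equipment itself, the section on additional cleaning says: "The additional cleaning will focus on specific shared medical equipment (Table 1"). Table 1 has eight lines but seven types, because drip stands are split into those in use and those in storage. All seven types are cleaned daily. The weekly frequency applies only to the vertical surfaces and pedestals of computers on wheels.

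Outcomes {12} defines the outcome per dot: "thoroughness of cleaning as being the proportion of dots that were completely removed".

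**The concern.** A drip stand, a commode and a computer keyboard need not be equally likely to be cleaned well. The protocol itself treats type as relevant, because it randomises the audit in order to obtain a variety of equipment. Since the audited item is picked by name, its type is known at no cost. A model that ignores it leaves any variation between types unexplained and gives up power that the data already hold.

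The audits are also described as the measure of fidelity of the additional cleaning, so their estimate will be used to interpret the infection result, whichever way that falls. A weaker analysis matters most if the improvement in cleaning is modest, which is where a reader would most want to know whether the intervention was delivered.

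**Working it through.** **No figure to reproduce.** The protocol gives no sample size, number of dots, expected proportion or power for the audits. Its sample size of 3960 belongs to the infection outcome. What follows from the text is 36 weeks / 2 = 18 audits per ward, and 18 × 10 wards = 180 ward-audits.

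**What a plain random draw covers.** With n items and seven equally likely types, the expected number of types present is 7 × (1 − (6/7)^n). For an assumed n = 8 this is 4.96, and all seven appear with probability 7! × 28 / 7^8 = 2.4%. For n = 14 the expected number is 6.19. A plain draw therefore usually gives some variety but rarely every type.

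**Simulation.** From the protocol: 10 wards, 18 audits each, two wards crossing over every 6 weeks, seven types. Assumed: 14 dots per audit, baseline log-odds −0.5, ward SD 0.3, evenly spaced type effects with SD 0.5, 1.0 or 1.5, and a true log-odds ratio of 0 or 0.25 (odds ratio 1.28). The model is binomial-logit with a binary intervention effect; ward is fitted as a fixed effect in place of the random intercept. There were 600 runs per setting, so the Monte Carlo standard error is about 0.9 points near 5% and 2.0 points near 50%.

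| Draw | Type SD | Type I error without / with type | Power without / with type |
|---|---|---|---|
| Independent | 0.5 | 4.8% / 4.3% | 69.3% / 72.5% |
| Independent | 1.0 | 3.7% / 5.7% | 57.0% / 65.7% |
| Independent | 1.5 | 5.5% / 4.7% | 46.0% / 59.5% |
| Stratified by type | 0.5 | 3.8% / 5.5% | 74.2% / 75.5% |
| Stratified by type | 1.0 | 1.7% / 4.2% | 59.7% / 68.2% |
| Stratified by type | 1.5 | 1.3% / 4.2% | 45.5% / 63.2% |
| Two types per audit | 0.5 | 9.2% / 5.2% | 71.3% / 72.5% |
| Two types per audit | 1.0 | 15.8% / 3.0% | 56.7% / 67.8% |
| Two types per audit | 1.5 | 21.2% / 5.3% | 47.7% / 57.2% |

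*Power.* With independent draws the loss is about 3, 9 and 14 points. With a stratified draw it is about 1, 9 and 18. Further runs with eight items per audit (seven when stratified) gave about 1 to 13 points. In the two-type rows power is not comparable, because the test without the term is oversized. For independent draws, the squared ratio of mean z-values expresses the loss as extra dots needed: (2.610/2.528)² = 1.07, (2.377/2.181)² = 1.19 and (2.213/1.799)² = 1.51.

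*Size of the estimate.* With independent draws and a true value of 0.25, the mean log-odds ratio without type was 0.235, 0.202 and 0.165. Averaging the seven type-specific probabilities first gives the marginal value directly. At SD 1.0 they average 0.4002 under control and 0.4497 under intervention, so logit(0.4497) − logit(0.4002) = 0.203. The same sum gives 0.236 at SD 0.5 and 0.166 at SD 1.5. The shrinkage is therefore almost wholly the move from a type-conditional to a marginal odds ratio.

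*Bias.* In every null setting the mean estimate was close to 0.

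*Why the type I error differs by draw.* With independent draws, mix is part of ordinary binomial error. With a stratified draw the mix is fixed, so the binomial variance is too large. With few types per audit, dots in an audit share a type and vary together, which a ward intercept cannot absorb. In the runs with eight items per audit, two or three types per audit gave about 6% to 16%.

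**The case against.** The strongest reply has four parts.

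- **Spread between types is assumed.** No passage gives cleaning rates by type. Table 1 does not show that they differ: all types are cleaned daily, and the times are for equipment groups. This stands, and it is why the size is given as a range.
- **The draw may already be stratified.** The protocol does not state the unit of the draw, the number of items or any stratification, and its aim of variety fits a constrained draw. This also stands, but it does not remove the point: under a stratified draw the model without type is conservative and still loses power.
- **An unadjusted comparison is legitimate.** Items are picked at random by someone outside data collection, and covariates are often left to an analysis plan. The comparison is valid. However, the protocol does set out the terms of this model, so a better-specified one is a fair suggestion.
- **A large effect would be found anyway.** This stands. With eight items per audit, eight equipment groups and a true odds ratio of 4, mean z was 8.97 without the term and 9.71 with it at SD 1.0, and 7.45 against 8.71 at SD 1.5.

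A reader might infer that chance differences in equipment mix could pass for a cleaning effect. The documents do not support that as a general statement. Selection is unrelated to trial phase, and with independent draws type I error was 3.7% to 5.5% without the term. Inflation needs audits concentrated on few types. That could arise if one item carries several dots (Table 1 lists several surfaces for a blood pressure machine), but the protocol does not say so. One type per audit would give 14% to 41%, but that contradicts the stated aim of variety.

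**Conclusion.** The point holds as one of efficiency. The audit model leaves out a covariate that is known for every item. If types differ in how well they are cleaned (assumed log-odds SD 0.5 to 1.5), this costs roughly 1 to 14 power points for a modest effect, with 18 in the stratified setting at the widest spread. It also makes the reported odds ratio a marginal one that lies closer to 1.

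It does not bias the estimate, and it does not break the 5% level under independent draws. The test is somewhat conservative under a stratified draw, and type I error reaches about 6% to 21% only if each audit covers two or three types. Nor is it exact to say that precision is lost: with independent draws the model standard error is slightly smaller without the term (0.092 to 0.093, against 0.096 to 0.113 with it). What is lost is power.

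The figures rest on the assumed number of dots, spread and effect size. Weight: low to moderate, since this is a secondary process outcome and a large improvement would be detected either way.

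**What to change.** In the FM audits analysis, model the individual audited item, with equipment type (the seven Table 1 types) as a fixed or random effect beside the ward intercept and intervention term. The type term is what helps: item-level analysis without it has the same likelihood, up to a constant, as the audit-level binomial model.

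In Sequence generation {16a}, stratify the random draw by Table 1 type so that each audit covers a variety of types by design. Make the two changes together, because stratifying the draw while leaving type out of the model makes the test conservative.

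The cost is one model term and a stratified draw list. The reported odds ratio becomes type-conditional, which should be stated. No new data or staff are needed, and by the Trial status section data collection had not begun.
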